## Introduction

Stroke is currently recognized as the second leading cause of disability and mortality worldwide (1), with acute ischemic stroke accounting for approximately 85% of cases (2). In China, the incidence of stroke has been increasing annually over the past 30 years, making it the leading cause of death in the country (3). Stroke is characterized by high incidence rates, high recurrence rates, high disability rates, and high case fatality rates (4). Acute ischemic stroke (AIS) refers to a group of syndromes caused by various factors leading to impaired blood supply to brain tissue (5). This impairment triggers a series of cascade reactions, resulting in ischemic and hypoxic necrosis in the brain, as well as neurological deficits in clinical practice (6). The current preferred treatment methods include intravenous thrombolysis and intravascular intervention therapy (7). However, treatment for AIS is often delayed due to factors such as low public awareness, a narrow thrombolysis time window, and strict eligibility criteria for thrombolysis. Only 21.5% of AIS patients in China arrive at the emergency department within 3 h of onset, and 12.6% are eligible for thrombolysis treatment, with fewer than 3% actually receiving it. The average interval between patient arrival at the emergency department and the administration of thrombolytic drugs is 116 min, significantly longer than in developed countries (8). Very few patients in China receive timely and effective thrombolytic therapy within the designated time window; therefore, it is essential for these patients to seek alternative treatments. Acute cerebral infarction is classified as a type of “stroke” in traditional Chinese medicine. Acupuncture, an important adjunctive treatment during the acute phase of cerebral infarction (9), has been shown to promote collateral circulation and improve brain circulation and metabolism to some extent (10). Currently, some scholars recommend initiating acupuncture treatment as soon as the patient’s vital signs stabilize (11). Therefore, in the early stages of acute ischemic stroke, when thrombolysis is no longer feasible and medical conditions are underdeveloped, acupuncture may offer timely intervention to mitigate the extent of cerebral infarction, reduce sequelae, and decrease the likelihood of functional disability, thereby conserving social resources (12).

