### Inclusion criteria

(1) Meets the diagnostic criteria for acute cerebral infarction as outlined in the “Guidelines for the Prevention and Treatment of Stroke in China” (2021 edition), and diagnosed through head CT or MRI examination;(2) Meets the diagnostic criteria for stroke as defined by Traditional Chinese Medicine (TCM);(3) Individuals experiencing their first stroke within 7 days of onset and are aged between 35 and 75 years;(4) NIHSS score ≥ 3 and ≤ 20, with no physical disability related to the study prior to disease onset;(5) Clear consciousness, defined as GCS score ≥ 13 points;(6) Individuals who voluntarily participate in this study and provide informed consent form.

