### Exclusion criteria

Patients who meet any of the following criteria will be excluded from the study:

(1) Transient ischemic attacks, subarachnoid hemorrhage, cerebral hemorrhage, or other similar conditions;(2) Patients requiring arterial or venous thrombolysis or thrombectomy based on their condition;(3) Individuals suffering from immune-related diseases, such as acute or chronic infections, tumors, and blood disorders, or who have severe organ dysfunction;(4) Individuals with severe cardiovascular dysfunction, upper gastrointestinal bleeding, intolerance to electroacupuncture, or those with pacemakers or stents;(5) Pregnant, pre-pregnant, or lactating individuals;(6) Family members or patients who exhibit poor initiative or lack cooperation;(7) Participants who have participated in other clinical trials within 1 month prior to this study.

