### Interventions

(1) Control group (conventional basic treatment): 33 patients

Standardized basic treatment will follow the “Chinese Guidelines for Stroke Prevention and Control” (2021 edition): ① Antiplatelet therapy: the use of antiplatelet aggregation drugs, including oral enteric-coated aspirin tablets (Bayer Medical and Health Co., Ltd., National Medical Approval No. J20171021) or oral clopidogrel bisulfate tablets (Lepu Pharmaceutical Co., Ltd., National Pharmaceutical Approval Letter H20123116); ② Lipid-regulating and plaque-stabilizing agents: oral atorvastatin calcium tablets (Beijing Jialin Pharmaceutical Co., Ltd., National Medical Approval No. H20093819). These medications will be administered continuously for 10 days. If patients have other underlying conditions, blood pressure, blood glucose levels, and water-electrolyte balance will be regulated based on individual circumstances.

(2) Acupuncture group (conventional basic therapy + acupuncture): 33 patients

① Basic treatment: Identical to that of the control group② Acupuncture treatment

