### Outcome measurement

Clinical indicators will be conducted uniformly by professional physicians or therapists. NIHSS scores will be assessed once before treatment (Day 1), during treatment (Day 5), and after treatment (Day 10). BMI and mRS scores will be assessed before treatment (Day 1) and after treatment (Day 10).

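### Entry up to 7 days after onset, with no exclusion for acupuncture already given for this stroke and an unclear one for reperfusion already given, can dilute the contrast the trial is built to measure

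*Protocol article*

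**What the plan says.** The protocol article's Inclusion criteria set the entry window: "Individuals experiencing their first stroke within 7 days of onset and are aged between 35 and 75 years".

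The Exclusion criteria have seven items. Three bear on earlier treatment or on acupuncture:

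- Item 2 removes "Patients requiring arterial or venous thrombolysis or thrombectomy based on their condition".
- Item 4 includes "intolerance to electroacupuncture, or those with pacemakers or stents". This is the only mention of acupuncture in the list, and it concerns tolerance, not earlier receipt.
- Item 7 removes "Participants who have participated in other clinical trials within 1 month prior to this study". This is the only rule that looks back in time.

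The Introduction notes that "some scholars recommend initiating acupuncture treatment as soon as the patient’s vital signs stabilize". It presents acupuncture as an option early after stroke, once thrombolysis can no longer be given.

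The Outcome measurement section fixes the primary measure: "NIHSS scores will be assessed once before treatment (Day 1), during treatment (Day 5), and after treatment (Day 10)". Under Blood serum index, the inflammatory and vascular markers are also taken from Day 1 onwards. Under Interventions, the comparator is "Control group (conventional basic treatment): 33 patients", consisting of antiplatelet and statin treatment with individual management of other conditions.

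**The concern.** The criteria describe the patient at enrolment and say little about what was given between onset and enrolment, which may be as long as 7 days. The trial takes place at a Chinese-medicine university hospital, and the Abstract calls acupuncture widely used in stroke care. A stable patient enrolled on day 6 after several needling sessions meets every printed criterion and may be allocated to the arm meant to go without acupuncture. Such patients weaken the acupuncture versus no-acupuncture contrast. Their Day 1 VEGF, TNF-α, IL-1β, endostatin and CD14 values may already reflect the treatment under study, which matters for a trial with a mechanistic aim.

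The reperfusion item has a related gap. A patient thrombolysed on day 0 and screened on day 3 no longer needs thrombolysis. Read literally, item 2 lets that patient in; read by its likely intent, it does not. Two screeners could decide differently.

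**Working it through.** **1. The plan's own figure.** Inputs from Sample size: means 12.61 and 7.53, so δ = 5.08; σ = 5.62; two-sided α = 0.05; power 0.90.

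n = 2 × (1.96 + 1.28)² × 5.62² / 5.08² = 25.7, so 26 per arm. With 20% dropout, 26 / 0.8 = 32.5, so 33 per arm and 66 in total. The stated size reproduces.

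**2. Dilution (assumption).** Suppose a share q of patients in both arms contributes no between-arm difference, because their response to acupuncture is already present at entry. The expected difference becomes 5.08 × (1 − q):

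- q = 10%: 4.57
- q = 20%: 4.06
- q = 30%: 3.56

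The documents give no value for q. A loss as large as q is a worst case, since it supposes that a previously needled patient gains nothing from ten further daily sessions.

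**3. Power.** Two-sample t-test, two-sided α = 0.05, noncentrality δ(1 − q)/σ × √(n/2), with σ held at 5.62:

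| q | 26 per arm | 33 per arm |
|---|---|---|
| 0 | 89% | 95% |
| 10% | 82% | 90% |
| 20% | 72% | 82% |
| 30% | 61% | 72% |

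The normal approximation that the plan's formula uses gives values 1 to 2 points higher (at q = 10% and 20%: 83% and 74% with 26 per arm, 91% and 84% with 33).

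**4. Sensitivity to the SD.** The plan's SD formula includes the difference between the group means. With the two stated SDs and equal groups of 63, the within-group pooled SD is √((4.04² + 5.86²)/2) = 5.03. With 5.03, power at q = 20% is about 82% with 26 per arm and 90% with 33.

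**5. Chance imbalance.** With 33 per arm and a prevalence p of prior exposure, the 95% range of the between-arm difference in prevalence is ±1.96 × √(2p(1 − p)/33):

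- p = 10%: ±14 percentage points
- p = 20%: ±19
- p = 30%: ±22

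These values of p are also assumptions.

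**6. Reperfusion.** The Introduction says that fewer than 3% of patients with acute ischemic stroke in China receive thrombolysis. Applied to 66 patients, 0.03 × 66 = 1.98, so about two or fewer. This national figure does not cover thrombectomy, but the stent exclusion in item 4 removes some endovascular cases.

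**The case against.** The strongest reply is that this is an omission in a condensed article. The full protocol may settle it, and nowhere does the article claim that patients are acupuncture-naive. That carries some weight. However, the article prints an itemised eligibility list, down to stents and poor cooperation, and earlier receipt of the experimental treatment helps define the study population. As printed, the list admits these patients.

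A reader might infer more than the documents support:

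- *That the comparison is biased.* It is not. Exposure before randomisation is balanced in expectation. Chance imbalance affects every baseline factor in a small trial with simple randomisation.
- *That the Day 1 baseline is invalid.* Day 1 precedes trial treatment and serves as a baseline whatever happened earlier. What it may lack is an acupuncture-naive meaning in some patients.
- *That the control arm is untreated or contaminated.* Controls receive basic treatment. Needling of controls during the 10 days would be a matter of concomitant treatment, which these criteria do not address in either direction.

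The likelihood of prior acupuncture is also inferred. The Introduction reports only that some authors recommend an early start, and the Discussion speaks of wide use for stroke sequelae, with acute-stage effects still poorly understood. Nothing shows that emergency inpatients have had several sessions before enrolment. This objection stands, and it is why the size is left open.

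Finally, item 2 can naturally be read to cover a patient whose stroke required reperfusion and who received it. That is probably the intent, but the wording does not say so.

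**Conclusion.** The point holds as a gap in the eligibility rules that is cheap to close. The printed criteria admit patients already needled for this stroke and, read literally, patients already reperfused, which sits badly with the target population in the Introduction. The consequences are possible dilution of the contrast, Day 1 values that are not acupuncture-naive in some patients, and chance imbalance.

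The loss cannot be estimated from the article. If 10% to 20% of the 5.08-point difference were lost, power at SD 5.62 would be about 82% to 72% with 26 evaluable per arm, and about 90% to 82% if all 33 are evaluable. The stated sample size therefore absorbs part of a modest dilution, and more of it if the within-group SD of 5.03 applies. The thrombolysis part is small on the article's own figure. The stronger conclusions, systematic bias or an unusable baseline, are not supported.

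**What to change.** Three changes:

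1. Add an exclusion: *acupuncture or electroacupuncture for the present stroke, given after onset and before randomisation*.
2. Reword exclusion 2 to *patients who have received, or require, arterial or venous thrombolysis or thrombectomy for the present stroke*, so that it agrees with the population described in the Introduction.
3. Check both on the Day 1 screening form.

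If the sponsor prefers to admit previously needled patients, the minimum is to say so and to record prior acupuncture (yes or no, number of sessions) as a baseline variable. That would show any imbalance but would not restore a diluted contrast.

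The cost is two lines in the criteria and two screening questions. Some late-presenting patients who have already been needled would be lost, so recruitment would be slightly slower.

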### Exclusion criteria

Patients who meet any of the following criteria will be excluded from the study:

(1) Transient ischemic attacks, subarachnoid hemorrhage, cerebral hemorrhage, or other similar conditions;(2) Patients requiring arterial or venous thrombolysis or thrombectomy based on their condition;(3) Individuals suffering from immune-related diseases, such as acute or chronic infections, tumors, and blood disorders, or who have severe organ dysfunction;(4) Individuals with severe cardiovascular dysfunction, upper gastrointestinal bleeding, intolerance to electroacupuncture, or those with pacemakers or stents;(5) Pregnant, pre-pregnant, or lactating individuals;(6) Family members or patients who exhibit poor initiative or lack cooperation;(7) Participants who have participated in other clinical trials within 1 month prior to this study.

### Termination criteria

Patients who meet any of the following criteria will be excluded from the study:

(1) Individuals who experience disease progression during the study that affects vital signs and requires transfer to the intensive care unit (ICU);(3) Individuals who experience serious adverse reactions or other events that impede recovery during the study;(4) Patients or family members who are unwilling to continue the clinical trial and wishing to withdraw for conciseness;(5) Individuals who exhibit intolerance to electroacupuncture or significant toxic side effects from medication during the treatment process;(6) Clinicians determine that other circumstances warrant termination of the study.

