### Data monitoring and statistical analysis

To minimize measurement bias arising from multiple evaluators, clinical indicator assessments and laboratory tests for each patient before, during, and after treatment will be conducted by the same specialized physician whenever possible. The physician evaluating the laboratory indicators will be blinded to the group assignments and treatment. To avoid missing or incorrect data, clinical and laboratory indicator evaluations will be conducted according to preset time points and entered into the electronic database promptly.

Data management and analysis will be performed using IBM SPSS Statistics Version 26 (IBM SPSS Inc., Chicago, United States). The principles of data processing are as follows: measurement data will be expressed as mean ± standard deviation (
$\bar{x}$
± S); if count data are normally distributed, the chi-square test will be used; if data in the two groups are normally distributed, t-test, repeated-measures analysis of variance (ANOVA), and multivariate linear regression will be used for comparative analyses; if count data are not normally distributed, the Mann–Whitney U test will be used; *p* < 0.05 will indicate statistically significant differences.

We will use the last observation carried forward (LOCF) method, which replaces missing data points with the patient’s last observed value. In order to provide a more comprehensive assessment of the treatment effects in this study, we will conduct both an intention-to-treat (ITT) analysis and a per-protocol (PP) analysis.

We will implement the Bonferroni correction during statistical analysis to rigorously control Type I error rates, thereby ensuring methodological stringency in accordance with your recommendation.

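### Removing patients from the study after randomisation, on grounds tied to outcome and partly to arm, is not reconciled with the promised intention-to-treat analysis

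*Protocol article*

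**What the plan says.** The Termination criteria section of the protocol article opens with "Patients who meet any of the following criteria will be excluded from the study". The Exclusion criteria section, which governs entry, opens with the same sentence. The events listed under Termination criteria, however, happen after enrolment:

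- "Individuals who experience disease progression during the study that affects vital signs and requires transfer to the intensive care unit (ICU";
- "Individuals who experience serious adverse reactions or other events that impede recovery during the study";
- "Individuals who exhibit intolerance to electroacupuncture or significant toxic side effects from medication during the treatment process";
- "Clinicians determine that other circumstances warrant termination of the study".

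Withdrawal by the patient or family is also listed and is not at issue here.

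The section Data monitoring and statistical analysis states "We will use the last observation carried forward (LOCF) method" and then "we will conduct both an intention-to-treat (ITT) analysis and a per-protocol (PP) analysis". The primary outcome is the NIHSS, and the Outcome measurement section gives its schedule: "NIHSS scores will be assessed once before treatment (Day 1), during treatment (Day 5), and after treatment (Day 10". The Follow-up section adds the Modified Barthel Index (MBI) and modified Rankin Scale (mRS) at 1 and 3 months after discharge. None of these sections says whether a patient who meets a termination criterion is still assessed.

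**The concern.** An ITT comparison rests on following everyone who was randomised. Here the stated rule ends participation for reasons bound up with the outcome.

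- **Outcome-related grounds.** Progression leading to intensive care, and serious events that impede recovery, are poor neurological courses. The abstract and the Discussion name prevention of further progression as an aim, so the patients who bear most directly on that aim are the ones whose Day 10 NIHSS and later MBI and mRS would not be collected.
- **An arm-specific ground.** The Interventions section gives electroacupuncture to one arm only, so intolerance to it can remove patients from that arm only. The medication-toxicity half of the same criterion applies to both arms.
- **A discretionary ground.** Under Random allocation, the attending physicians and acupuncture therapists keep the envelopes and treat according to them. The Blinding section covers outcome assessors, statisticians and laboratory staff. The clinicians who may invoke the open-ended criterion are not described as blinded.

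This is a rule that the article states, not detail left to a fuller document. Assessments that are never made cannot be recovered at the analysis stage.

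**Working it through.** **The plan's own figure.** The sample size reproduces: 2 × (1.96 + 1.28)² × 5.62² / 5.08² = 25.7, so 26 per group; 26 / 0.8 = 32.5, so 33 per group and 66 in total. The point does not depend on it. The 20% allowance replaces lost precision (power is about 0.90 with 26 per arm and 0.96 with all 33), but it does not correct for which patients are lost.

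**Illustration.** The article gives no rates of deterioration or intolerance, so these inputs are assumptions: deteriorating patients end 6 NIHSS points above baseline, the others end 3 points below, and the two arms differ only in the share p that deteriorates. Differences are acupuncture minus control in mean change; positive means worse on acupuncture.

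- All patients observed: mean change = 6p − 3(1 − p).
- Excluded: only non-deteriorating patients remain, so mean change = −3 in both arms.
- LOCF from Day 1: deteriorating patients count as 0, so mean change = −3(1 − p).

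| Share deteriorating (acupuncture, control) | All observed | Excluded | LOCF from Day 1 |
|---|---|---|---|
| 20%, 10% | −1.2 − (−2.1) = +0.9 | −3 − (−3) = 0.0 | −2.4 − (−2.7) = +0.3 |
| 10%, 20% | −2.1 − (−1.2) = −0.9 | 0.0 | −2.7 − (−2.4) = −0.3 |

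In the first row a harm of 0.9 points disappears under exclusion and shrinks by two thirds under LOCF. In the second row a benefit of 0.9 points is hidden to the same extent. If a Day 5 score is carried instead and shows a change c between −3 and 0, LOCF gives 0.10 × (c + 3) in the first row, that is, between 0.0 and 0.3.

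**Sensitivity.** In general, the bias from exclusion = −(excess NIHSS of removed patients) × (share removed in acupuncture − share removed in control). With an excess of 4 to 12 points:

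- 10% and 10% removed: no bias;
- 15% and 5% removed: −0.4 to −1.2, favouring acupuncture;
- 5% and 15% removed: +0.4 to +1.2, against acupuncture.

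**The arm-specific ground.** Assume no effect on deterioration, 10% deteriorating in each arm, and 10% of acupuncture patients intolerant.

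- If intolerant patients who do not deteriorate would end 3 points worse than the others, excluding them hides about 0.9 × 0.10 × 3 = 0.27 points to the benefit of acupuncture.
- If they do no worse, the bias is 0.
- If they would have recovered 3 points like the rest but are carried forward from Day 1, that recovery is lost, and the error is about 0.9 × 0.10 × 3 = 0.27 points against acupuncture.

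So even the one-sided ground has no fixed direction.

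**Scale.** A shift of 0.9 points is 0.9 / 5.08 = 18% of the planned difference. With 26 per arm the standard error is 5.62 × √(2/26) = 1.56 points, so 0.9 is about 0.6 of a standard error.

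**The case against.** The strongest defence is that the section is headed as termination, not as an analysis rule, and that its lead sentence may simply have been carried over from the entry criteria. On that reading participation ends, ITT with LOCF retains the patient (everyone has a Day 1 NIHSS and some have Day 5), and only the per-protocol set drops the patient. No section removes anyone from the ITT set. This stands as far as it goes: a reader might infer a flat contradiction, or that ITT cannot be carried out, and the article does not support either. But this reading still leaves the worsening uncounted, as the LOCF column shows.

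A reader might also infer that the exclusions favour acupuncture. That is not established. Most grounds act in both arms, and swapping the assumed rates reverses the sign. One can construct a spurious benefit of about 0.34 to 0.37 points on raw Day 10 scores by assuming that 10% of acupuncture patients are intolerant and all lie in the more severe half at baseline (baseline mean 9, SD 4.5, limited to 3–20). But that is baseline imbalance: it is 0 on change from baseline, and becomes about 0.27 against acupuncture under ITT with LOCF from Day 1.

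Three further points are fair. Intolerance to electroacupuncture is already an entry exclusion, so the on-treatment rate may be low. Adverse reactions are recorded and events graded by CTCAE, so harm would not vanish from the trial, although it could be missing from the NIHSS comparison. And naming the primary analysis set may be left to an analysis plan; that is not criticised here.

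**Conclusion.** The point holds in a limited form. The termination rule, as written, ends participation after randomisation on grounds that depend on outcome and partly on arm, and it is not reconciled with the ITT analysis promised in the statistical section. LOCF does not close the gap. The NIHSS comparison can be biased in either direction, and a harm or a benefit that acts through deterioration can be masked. The size is unknown: the 0.9-point example, and the range of 0.4 to 1.2 points in either direction, rest on assumed rates and assumed severity. These shifts are modest beside the planned difference of 5.08 points, but they would matter if the true effect is smaller. Not knowing the direction does not lessen the need to act, since the missing assessments cannot be reconstructed later.

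**What to change.** Reconcile Termination criteria with Data monitoring and statistical analysis by separating two things: stopping study treatment, and leaving the study.

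- A patient who meets a termination criterion stays in follow-up unless consent to further data collection is withdrawn.
- NIHSS is still taken at Days 5 and 10, and MBI and mRS at Day 10 (Outcome measurement prints BMI where MBI appears to be meant) and at 1 and 3 months, where possible.
- These patients are analysed in the ITT set in the arm to which they were randomised. The termination criteria remove them from the per-protocol set only.
- LOCF is then needed only where an assessment could not be made.

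The cost is a change of wording and a few assessments of sicker patients. The trial is single-centre, so many of these patients are probably still in the same hospital, although the article does not say so. The sample size is unchanged. When treatment itself should stop is not questioned here.
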